Therefore, the primary goal of the TEAMS (TElerehabilitation And Multiple Sclerosis) is to implement a single-blind, RCT designed to compare the effectiveness of an 8-week home-based telerehab VR program with conventional therapy in PwMS with manual dexterity difficulties. Secondary aims include (a) evaluating the impact of the programs on quality of life after the intervention and follow-up 1 month later and (b) evaluating the impact of the programs on adherence and satisfaction. A tertiary aim will be to generate effect sizes which can be used to power a larger clinical trial aimed at improving upper limb functional activities via telerehab in PwMS in Italy and Israel. We hypothesize that there will be no difference in outcomes between a home-based telerehab VR training program aimed at improving functional activities of the upper limbs compared with a conventional clinic-based program after the intervention and follow-up 1 month later. We also intend to corroborate a secondary hypothesis that performing the telerehab VR training will lead to better outcomes in quality of life and adherence to upper limb exercise.

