##### Brief Repeatable Battery of Neuropsychological Tests (BRB-N) (collected only at baseline T0)

The BRB-N are sensitive measurement tools aiding in identifying cognitive impairment in PwMS. This battery of tests includes the Selective Reminding Test, the 10/36 Spatial Recall Test, the Symbol Digit Modalities Test, the Paced Auditory Serial Addition Test, and the Word List Generation Test [40]. Cognitive status will be collected only at baseline*.*

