### Statistical analysis

Data analysis will be performed by the SPSS 25.0 program. The data will be initially examined for normality violations, outliers, errors, and patterns of missing values; missing data will be replaced by multiple imputation techniques found in the SPSS. In the event of exacerbations, the analysis will be conducted with and without the individuals who had relapsed in order to identify any untoward effects on the outcomes. The data analysis itself will follow intent-to-treat principles. The effect of the intervention on the NHPT (aim 1), ARAT (aim 1), MAM-36 (aim 1), SF-36 (aim 2), and adherence and user satisfaction (aim 3) will be examined using the Condition × Time mixed model multivariate analysis of variance (MANOVA) followed by an inspection of the univariate F-ratios. Conditions will be a between-subjects factor and time and a within-subjects factor. Interactions and main effects will be further calculated using post hoc analyses with a correction of alpha. Effect sizes associated with univariate *F*-statistics will be expressed as eta-squared (*η*^2^), and effect sizes based on a difference in mean scores will be expressed as Cohen’s *d*. We will include cognitive scores (BRB-N) as covariates in all final statistical analyses.

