## Discussion

The TEAMS project has tremendous potential to improve the quality of evidence and informed decisions of functional upper limb activities in PwMS. The project addresses the needs of PwMS [2, 6, 8], specifically, if they are provided access to functional upper limb exercises and does the location where the exercises are performed impact their outcomes? Is it necessary to travel to a healthcare facility with access to equipment and MS experts in order to benefit from upper limb exercises or can the PwMS safely and effectively exercise in their own home, if provided with expert guidance? We will compare a conventional healthcare facility training program with a VR telerehab home-based program. This information will impact the PwMS’s informed decisions as to how to spend their time and potentially limited resources.

If comparable results are found between the treatments in improving upper limb outcomes, this would suggest that PwMS can choose the program that best meets their personal needs, e.g., financial concerns, transportation, or accessibility issues. Secondly, this information can be used by healthcare providers and medical professionals by developing upper limb exercise programs that will most likely succeed and can then be distributed to neurologists and other medical providers. Finally, increasing an individuals’ accessibility to upper limb exercise options may prevent or slow the decline of disability, increase independence in ADL functions, and help maintain a better quality of life.

The telerehab VR proposal for restoring upper limb functional activities in PwMS is an expansion of a project originally developed by the University of Cagliari (Italy) that included a feasibility study which produced encouraging results. The following goals were reached during the initial phase: (1) recruitment of technological developers and MS professionals, (2) definition of upper limb functional difficulties and relevant rehabilitation exercises of the population target, and (3) development of a hardware-software VR platform based on low-cost tools, encouraging self-practice of functional exercises of the upper limb. Important elements include a user-friendly system that can be easily assembled, used in the home and be monitored from a distance by a medical/rehab professional.

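### BRB-N covariates are not stated to be mean-centred, so the Time F-ratio and its eta-squared may describe a patient at covariate value zero instead of the average participant

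*Protocol article*

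**What the plan says.** The Statistical analysis section plans a "Condition × Time mixed model multivariate analysis of variance (MANOVA) followed by an inspection of the univariate F-ratios" for the NHPT, ARAT, MAM-36, SF-36, adherence and satisfaction. Time (T0, T1, T2) is the within-subject factor. Main effects are part of the reading: "Interactions and main effects will be further calculated using post hoc analyses with a correction of alpha". Effect sizes for the univariate F-statistics are to be given as eta-squared, and those for mean differences as Cohen's d. The section ends: "We will include cognitive scores (BRB-N) as covariates in all final statistical analyses".

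The BRB-N section lists five tests and adds "Cognitive status will be collected only at baseline". The covariates are therefore constant over time within a patient. On software the article says only "Data analysis will be performed by the SPSS 25.0 program". It does not state whether scores enter raw, as z-scores, as a composite or centred, or how many enter.

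The primary hypothesis in the Background concerns the arms: "We hypothesize that there will be no difference in outcomes between a home-based telerehab VR training program" and conventional therapy. The Discussion builds its message on a wider condition: "If comparable results are found between the treatments in improving upper limb outcomes".

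**The concern.** In a repeated-measures MANOVA with a baseline covariate, each time contrast has its own intercept and its own slope on the covariate. The Time test is the test of that intercept, which is the mean change where every covariate equals zero. If the scores enter as collected, that point is a patient scoring zero on every BRB-N test entered. The exclusion criteria remove patients with a Mini-Mental score below 21, so such a patient is in practice outside the sample. If norm-based z-scores are used, zero is the normative person, who is not the average trial participant either.

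Both arms are active and the hypothesis is no difference, so two programmes that do nothing would satisfy it equally well. The between-arm test cannot show that patients improved. Among the planned F-tests, only Time speaks to that. A Time F-ratio taken at the wrong point could miss a real gain in both arms. Where change depends on cognition, it could also be significant although the average change is zero. The eta-squared reported for Time would be off for the same reason, on every outcome analysed this way. It could also disagree with follow-up comparisons evaluated at the covariate mean.

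**Working it through.** **The plan's own figures.** The article gives no power figure for the Time test, so there is none to reproduce. Its sample size (24, 80% power, 5% alpha, r-squared 0.50) cannot be rebuilt because no SD is given. Worked backwards at two-sided 5%, 12 per arm detects (1.960 + 0.842) × √(2/12) × √0.50 = 0.81 SD between arms. The present point does not depend on this.

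**Step 1: what the Time test tests.** For time contrast c (T1−T0 or T2−T0), with arm G coded ±0.5 and covariates Xⱼ:

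D_c = α_c + γ_c·G + Σ β_cj·Xⱼ + error.

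The Time test is H₀: α_c = 0 for both contrasts, that is, no change at X = 0. After centring, the intercept becomes α_c + Σ β_cj·X̄ⱼ, the change at the sample mean. The two nulls coincide only if Σ β_cj·X̄ⱼ = 0 for each contrast, for example when change is unrelated to cognition. Condition × Time is the test of γ_c. Shifting X moves only the intercept, so γ_c and its F-ratio are unchanged.

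**Step 2: loss of precision.** With m = mean/SD of a score, the standard error of the intercept is multiplied by about:

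- one score: √(1 + m²);
- five scores with common correlation 0.4: √(1 + m² × 5/2.6), where 2.6 = 1 + 4 × 0.4.

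| m | one score | five scores |
|---|---|---|
| 1.5 | 1.8 | 2.3 |
| 2 | 2.2 | 2.9 |
| 3 | 3.2 | 4.3 |
| 4 | 4.1 | 5.6 |

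The document gives no BRB-N means or SDs, so the range of m is an assumption. For norm-based z-scores, m is the distance of the sample mean from the norm in sample SDs. That may be smaller than the range tabulated.

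**Step 3: power.** Simulation assumptions: 24 patients, 12 per arm; correlation 0.8 between visits; a true gain of 0.4 SD in both arms at T1 and T2; change unrelated to cognition; multivariate Time test at 5%. Where repeated runs differed, the range is shown.

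| m | one score, uncentred | five scores, uncentred |
|---|---|---|
| 1.5 | 34% | 17-19% |
| 2 | 22-25% | 12-13% |
| 3 | 14% | 8-10% |
| 4 | 9-11% | 7% |

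Centred, power is about 83-86% throughout.

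**Step 4: rejection when average change is zero.** Same design, with cognition explaining 10% of the variance in change:

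- one score: about 22-29% uncentred;
- five scores, one of them driving change: about 13-15% uncentred;
- centred: about 6%.

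If no patient changes at all, the rate is about 5% either way.

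**Step 5: a second parameterisation.** A separate simulation used univariate F-tests in seconds. Assumed values: between-patient SD 6 s, residual SD 3 s, mean gain 3 s, score means of about 2.9 to 3.7 SDs. With change unrelated to cognition, Time power was 14% (one score) and about 10% (five), against 94% centred. With change rising or falling by 1 s per SD of one score, uncentred power ranged from 5% to 51% (one score) and from 5% to 23% (five), against 94% centred. Condition × Time p-values with raw and centred scores agreed to about 1e-13.

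**The case against.** Five things can fairly be said against the point.

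- **Raw entry is not stated.** A reader might infer that the plan specifies raw scores. It does not; it is silent on scaling, and a condensed article may leave coding to a fuller document. This stands as a limit, and the point is conditional on it. It does not dispose of the point: following the sentence literally in the named model gives the wrong Time test.
- **The SPSS procedure is not named.** A mixed model with covariates as main effects only, without Time × covariate terms, would leave the Time test unchanged. That is true. But the text names MANOVA with univariate F-ratios and eta-squared, and in a MANOVA separate covariate slopes per visit are built in.
- **The primary question is untouched.** A reader might infer that the between-programme comparison is compromised. It is not: Condition × Time is identical with raw or centred scores. Moreover, the Background states no hypothesis of average change over time. With no untreated arm, even a correct Time test is a before-after comparison that cannot by itself credit the programmes.
- **Other measures of change are planned.** Post hoc comparisons evaluated at covariate means, and Cohen's d from differences in mean scores, need not be affected. This stands. What remains is the Time F-ratio, its eta-squared and possible disagreement with those follow-ups.
- **The sizes are assumed.** No BRB-N values, visit correlation or cognition-change relation appear in the document. The mechanism does not rest on these figures; the percentages do.

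**Conclusion.** The point holds in a limited, conditional form. If BRB-N scores enter the MANOVA as collected or as norm-based z-scores, the Time F-ratio and its eta-squared refer to covariate value zero. Under the assumptions above for scores as collected, power to detect a 0.4-SD gain in both arms drops from about 85% to roughly 10-34% with one score, or 7-19% with five.

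A reader might go further and infer that the plan inflates false positives in general. The calculations do not support that. Excess rejection requires change to depend on cognition: about 22-29% (one score) or 13-15% (five) against about 6% centred, when cognition explains about 10% of the variance in change. Without any change in any patient the rate stays at 5%.

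This is therefore a correction to a supporting test of improvement over time. It is worth making because the Discussion's message speaks of improvement as well as comparability, and because the correction costs nothing.

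**What to change.** Replace the covariate sentence in the Statistical analysis section with: *BRB-N scores enter as covariates after centring each at the overall sample mean, so that the Time effect and its effect size refer to the average participant.* If norm-based z-scores are used, re-centre those at the sample mean as well.

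Alternatively, take the Time test and its eta-squared from the model without covariates, and keep BRB-N for the Condition × Time contrast.

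The cost is one sentence and, for centring, one compute step in SPSS. No extra patients or data are needed, and centring leaves the Condition × Time result unchanged.

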### Participants

In total, 24 individuals with MS will be recruited from the two participating MS centers (12 from each center). Recruitment of participants will be handled by advertisement and awareness of the trial through the medical staff of each participating center.

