#### Sample size

The sample size is based on Julious’s [31] recommendation that the rule of thumb for a pilot study is a sample size of 12 subjects per group. The justifications for this sample size are based on rationale relating to feasibility, mean and variance precision, regulatory considerations, and the expected change in the study’s primary outcome measure (NHPT). According to the literature, a 20% change in the NHPT demonstrates a clinically meaningful worsening in PwMS [32]. In our study, power will be set at 80% and alpha at 5%. Therefore, 24 subjects (12 in each group) will be required in order to detect differences between the two treatment groups (assuming non-inferiority with moderate correlations among covariates, *r*-squared = 0.50).

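### With 24 patients, the final models adjust for a five-test cognitive battery and not for baseline NHPT, which widens the primary interval unless cognition predicts change in NHPT

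*Protocol article*

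**What the plan says.** - **Covariates.** The Statistical analysis section commits to this: "We will include cognitive scores (BRB-N) as covariates in all final statistical analyses". It names no other covariate.
- **Battery.** The BRB-N section reads: "This battery of tests includes the Selective Reminding Test, the 10/36 Spatial Recall Test, the Symbol Digit Modalities Test". It goes on to two further tests, five in all. No composite or number of scores is fixed.
- **Model.** A Condition × Time MANOVA, followed by univariate F-ratios, is applied to NHPT, ARAT, MAM-36, SF-36, adherence and satisfaction, each labelled with an aim. The factors are described thus: "Conditions will be a between-subjects factor and time and a within-subjects factor". NHPT is measured at T0, T1 and T2, so its baseline is a level of Time and not a covariate.
- **Size.** The Participants section states: "24 individuals with MS will be recruited from the two participating MS centers (12 from each center". The Sample size section gives 12 per arm.
- **Covariate credit.** The Sample size section takes an r-squared of 0.50, "assuming non-inferiority with moderate correlations among covariates", without saying which covariates supply it.
- **Timing.** The Outcomes section lists adherence and satisfaction under a heading that gives all three visits. The adherence text itself places the assessment at the end of the intervention phase, and the satisfaction questionnaire concerns the training received.

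**The concern.** At 12 per arm each covariate must earn its place. Here the only adjustment goes to variables for which the article states no link to change in peg-test time. The usual strong predictor of a post-treatment value, its own baseline, is not used as a covariate. The primary hypothesis is no difference and the sample size speaks of non-inferiority, so the width of the NHPT interval decides what the trial can say. A wide interval or a weak test makes a non-significant result easy to misread as comparability. The article also wants effect sizes for a larger trial, and these would carry the same loss of precision.

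**Working it through.** **1. The plan's own figure.** The inputs from Sample size are: "In our study, power will be set at 80% and alpha at 5"%; "a 20% change in the NHPT demonstrates a clinically meaningful worsening in PwMS"; r-squared 0.50; 12 per arm. No SD is given, so 24 cannot be reproduced as a power result; it matches the pilot rule of thumb cited there. Treat 20% of the mean as the margin (an assumption) and use n per arm = 2(z_α + z_β)² × SD² × (1 − R²) / margin². With one-sided α of 0.025, (1.960 + 0.842)² = 7.85. Then n = 12 requires residual SD / margin = √(12 / 15.70) = 0.874.
- Without covariate credit, the coefficient of variation (CV) must be about 0.2 × 0.874 = 0.17.
- With R² = 0.50, it may be 0.17 / √0.5, about 0.25.

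The credit therefore matters, but the only covariates the analysis names are the BRB-N scores.

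**2. Interval width.** Take the T1 − T0 contrast in units of the NHPT SD, N = 24, no dropout, k covariates:

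half-width = t(0.975, 22 − k) × √[V × (2/12) × 21/(21 − k)]

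V = 2(1 − ρ) for change from T0, and 1 − ρ² for baseline-adjusted ANCOVA. The factor 21/(21 − k) is the average cost of estimating k covariates. The covariates are taken as unrelated to the outcome. ρ is the baseline-to-T1 correlation, which is not in the article. At ρ = 0.707 (ρ² = 0.50):

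| Model | k | error df | t | V | half-width |
|---|---|---|---|---|---|
| Change, 5 BRB-N | 5 | 17 | 2.110 | 0.586 | 0.755 |
| Change, no covariate | 0 | 22 | 2.074 | 0.586 | 0.648 |
| ANCOVA, baseline | 1 | 21 | 2.080 | 0.500 | 0.615 |
| ANCOVA, baseline + centre | 2 | 20 | 2.086 | 0.500 | 0.633 |

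- Planned model against baseline + centre: 0.755 / 0.633 = 1.19, like needing 1.19² = 1.42 times the patients. The ratio is 1.27 at ρ = 0.5 and 1.16 at ρ = 0.8. Simulation gave about 1.22, 1.30 and 1.18 at ρ = 0.707, 0.5 and 0.8.
- BRB-N alone: 0.755 / 0.648 = 1.17, whatever ρ is.
- Change against baseline ANCOVA, no BRB-N: 0.648 / 0.615 = 1.05 (1.12 at ρ = 0.5, 1.03 at ρ = 0.8).
- Adding centre: 0.633 / 0.615 = 1.03, so it gives no gain in width.

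**3. Break-even.** The five scores repay their cost when 1 − R² = 1 / 1.1655² = 0.736, that is, when they explain about 26% of the variance in NHPT change.

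**4. Omnibus power.** An effect that ANCOVA (1 and 21 df) detects with 80% power has noncentrality 8.63. Place it in one contrast, uncorrelated with the rest. Each outcome at three visits gives two contrasts; denominator df = error df − contrasts + 1.

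| Outcomes in the MANOVA | Contrasts | No covariates (22 df) | 5 covariates (17 df) | 5 covariates, noncentrality / 1.3125 |
|---|---|---|---|---|
| NHPT, ARAT, MAM-36, SF-36 total | 8 | 0.33 | 0.27 | 0.21 |
| Aim 1 only: NHPT, ARAT, MAM-36 | 6 | 0.41 | 0.36 | 0.28 |

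**5. Can it be fitted?** Error df must be at least the number of contrasts. With five covariates (17 df), four total scores need 8 and fit. If all outcomes go into one model and SF-36 enters as eight scales (an assumption), 11 outcomes need 22 and the test cannot be computed.

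**The case against.** Several points on the other side stand.

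- **BRB-N may predict change, or be summarised.** If the five scores explain 10% or 20% of the change variance, the excess over baseline + centre ANCOVA at ρ = 0.707 falls from 19% to 13% or 7%. One summary score would cost a single degree of freedom. An unseen analysis plan may fix this, but the article's wording names the scores without limit and offers no evidence of a link.
- **Baseline is not ignored.** T0 is in the model as a level of Time. That choice alone costs only about 3% to 12% at ρ = 0.8 to 0.5; most of the loss comes from the BRB-N scores.
- **One MANOVA per aim is a natural reading**, because each outcome carries an aim label. Then the no-difference outcomes are not pooled with quality of life, where VR is expected to do better, and omnibus power is 0.28 to 0.41. That is still weak for a single primary outcome. The text also does not say that a non-significant omnibus stops testing.

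A reader might infer more than the article supports:

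- The number of MANOVA outcomes does not widen the NHPT interval. It costs degrees of freedom only in the multivariate test.
- The missing centre term does not widen it either. A stable centre difference cancels in change from T0, and adding centre changed the width by about 3% in the formula and roughly nothing in simulation.
- The model is not impossible to fit. That depends on an unstated choice such as entering SF-36 subscales.
- The article does not show that an r-squared of 0.50 is out of reach, only that it is not tied to any NHPT-related covariate.

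**Conclusion.** The point holds in this limited form. The only named covariates are scores from a five-test battery with no composite fixed, in an analysis of 24 patients, and baseline NHPT is not a covariate. The five scores cost about 17% in interval width unless they explain about a quarter of the variance in NHPT change. Against ANCOVA on baseline NHPT and centre, the planned interval is about 16% to 27% wider. These figures assume ρ from 0.8 to 0.5, five scores, no dropout, and BRB-N unrelated to NHPT change, so they are the unfavourable end for BRB-N. The omnibus test has power of about 0.2 to 0.4 for an NHPT effect that ANCOVA detects with 80%, under the one-contrast assumption. Separately from precision, adherence and satisfaction have no T0 value and cannot be analysed as Condition × Time as written. This is an inexpensive improvement to make, not a fatal flaw.

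**What to change.** - **NHPT:** analyse it alone by ANCOVA or a linear mixed model with arm, baseline NHPT and centre, and make T1 the primary contrast. Centre is there to reflect the two-centre design, not for precision.
- **ARAT, MAM-36, SF-36:** model each separately in the same way.
- **Adherence and satisfaction:** compare the arms after the intervention only.
- **BRB-N:** use it to describe the groups at baseline, or enter one pre-named summary score in a sensitivity analysis.
- **Sample size text:** name the covariate behind the r-squared of 0.50, so that it agrees with the analysis.

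The cost is wording. Baseline NHPT and centre are already recorded, and the article says that the trial has not begun. The downside is that the main model no longer carries full cognitive adjustment.

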### Roles and mode of integration between the teams

Data will be shared throughout the project by personal meetings, Skype™ video calls, conference calls, and e-mail correspondence. Specifically, the Italian group will be responsible for designing and implementing three new VR scenarios relating to functional activities of the upper limb. The new VR scenarios will be planned in conjunction with the Israel group who will also play an active role in the quality assessment procedures of the developed elements. Both groups will participate equally in the pilot RCT. Roles include recruitment and guidance of patients and therapists, implementing the telerehab VR system in the patient’s home with multi-layer security, end-to-end encryption, assessment of outcome measures, and data collection. Both sites will contribute to the analysis and interpretation of data and dissemination of the findings. An additional role of the Israel team will be to prepare a user manual detailing how to use the system and providing clinical guidelines/recommendations for both the therapist and patient. Both groups will be responsible for data entry, coding, security and storage. No anticipated harm is expected; therefore, a data monitoring committee is not required. However, an independent biostatistician will be involved in the data analysis. Periodic reports on progress of the trial will be provided to the funding bodies. There is no intended use of professional writers.

